#### Interim analyses regarding confirmatory analysis

An interim analysis will be performed as approximately a midcourse analysis with the objective of checking the assumptions of the initial sample size calculation. There is no α spending prespecified at the planned interim analysis. In cases where the interim analysis results in substantial differences from the assumptions at the planning stage, the assumptions will be revised and a sample size recalculation will be performed. The sample size recalculation will be based on the conditional rejection probability approach (see next section). If a sample size modification deems advisable, the study protocol will be amended.

Calculations for sequential analyses regarding the primary confirmatory analysis will be done in the Brownian motion model. Values of a Brownian motion are approximately resembled based on the accumulating data and applying the inverse normal transformation of the (exact) one-sided *p* values at interim and final analyses followed by multiplication with the square root of the information time. The information time is approximated by$$ \frac{{\mathrm{n}}_{\mathrm{IC},\mathrm{H}\mathrm{A},\mathrm{I}}\cdot {\mathrm{n}}_{\mathrm{IC},\mathrm{H}\mathrm{E}\mathrm{S},\mathrm{I}}}{{\mathrm{n}}_{\mathrm{IC},\mathrm{H}\mathrm{A},\mathrm{I}}+{\mathrm{n}}_{\mathrm{IC},\mathrm{H}\mathrm{E}\mathrm{S},\mathrm{I}}+1}+\frac{{\mathrm{n}}_{\mathrm{NB},\mathrm{H}\mathrm{A},\mathrm{I}}\cdot {\mathrm{n}}_{\mathrm{NB},\mathrm{H}\mathrm{E}\mathrm{S},\mathrm{I}}}{{\mathrm{n}}_{\mathrm{NB},\mathrm{H}\mathrm{A},\mathrm{I}}+{\mathrm{n}}_{\mathrm{NB},\mathrm{H}\mathrm{E}\mathrm{S},\mathrm{I}}+1} $$where n_S,T,I_ denotes the number of patients with assessed primary endpoint in stratum S (S = IC for ileal conduit or S = NB for neobladder) and treatment group T (T = HA or T = HES) at an arbitrary time during the course of the trial. Alternatively, a proportional information time scale may be used (e.g., by multiplication by a factor of 4).

#### Modifications of the statistical design for confirmatory analysis

To keep the type I error level in the case of a design modification at any time during the course of the trial, the Conditional Rejection Probability approach of Müller and Schäfer will be applied [21, 22]. Thereby, as described in the preceding section, the calculations will be based on the Brownian motion approximation. In the case of a modification of the statistical design (e.g., a sample size recalculation), the trial protocol will be amended.

#### Power considerations and sample size calculation

Three parameters will influence the sample size of the study, in which we will use the Mann-Whitney-Wilcoxon test for the statistical decision based on a fixed-sample design: the level of significance, the power of the two-sided test and the probability that an observation X_AlbuCyst_ in the HA group is less than an observation X_VoluCyst_ in the HES group. For sample size planning, no stratification and approximately normally distributed data for log-transformed cystatin C values and calculated log-transformed GFR values are assumed. The location parameter and standard deviation of cystatin C at baseline are assumed to be 0.9 mg/L and 0.2 mg/L, respectively, based on the publication by Evangelopoulos and colleagues [23]. Thereby we consider the older patient groups and greater variability because subgroups are pooled and study patients did not represent a healthy population.

For sample size calculation, the value of 0.2222 for the standard deviation of the difference at day 90 minus baseline of the log-normal transformed cystatin C values is specified in both treatment groups. There are two arguments for this specification. First, the value is suggested to be conservative in the four groups (two treatments times two measurement time points) considered in the statistical analyses. Second, adjusting for baseline values by using cystatin C values at day 90 relative to the same patients’ value at baseline is suggested to reduce rather than to increase the standard deviation.

An increase of the GFR by the factor 1.2 due to HA compared with HES would be clinically meaningful and worthwhile to be detected as statistically significant difference at a two-sided type I error level of α = 5 % with a statistical power of 1 − β = 80 %. For the interpretation of the increase of the GFR by the factor 1.2 consider, for example, a patient with a Cystatin C value of 0.9 mg/L. This value results in a calculated GFR at baseline between 86 and 87 ml/min. Then, the factor 1.2 would mean an increase of GFR at day 90 from 60 to 72 ml/min, from 65 to 78 ml/min, or from 70 to 84 ml/min.

The factor of 1.2 with respect to GFR transfers to the detectable difference of 0.1368 for the log-transformed (natural logarithm) Cystatin C values when using the conservative formula where the exponent is −1.333.

The detectable difference and the specified standard deviation correspond to the probability of$$ \mathrm{P}\left({\mathrm{X}}_{\mathrm{AlbuCyst}}<{\mathrm{X}}_{\mathrm{VoluCyst}}\right)=0.6683. $$With a sample size of 47 in each group, the non-stratified Mann-Whitney-Wilcoxon test at a 0.05 two-sided significance level will have 80 % power to detect a probability of 0.6683 that an observation X_AlbuCyst_ is less than an observation X_VoluCyst_. This means that n = 94 assessed patients are required in total to achieve the desired power.

On the basis of our experience with patient compliance in previous studies and routine treatment, we expect a dropout rate of about 10 %. Thus, adjusting for slight random imbalances in allocation to the treatment groups, a total of 105 patients (50–55 in each treatment group) have to be enrolled.

It has to be taken into consideration that about 50 % of patients fulfilling the inclusion criteria for this trial might refuse to give their informed consent to participate; we therefore expect to screen a total of about 210 patients for eligibility.

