### Statistical planning and analysis

#### Statistical analyses

The primary efficacy analysis statistically tests superiority of HA versus HES at an α significance level of 5 % (two-sided, simultaneously testing both sides at a level of 2.5 %) with respect to the primary endpoint.

The primary endpoint is expected to be non-normally distributed. After logarithm transformation, the primary endpoint may not be normally distributed. Thus, the corresponding statistical null hypothesis is the hypothesis that the distribution functions of the endpoint in the HA group and the HES group are equal and will be tested non-parametrically with the Mann-Whitney-Wilcoxon test to detect directed differences of the distributions. The Mann-Whitney-Wilcoxon test will be applied. The one-sided *p* value will be calculated, if possible, using Fisher’s exact test.

The primary endpoint adjusts in a specific way for the preoperative cystatin C values. At the planning stage, the Mann-Whitney-Wilcoxon test will be applied in the stratified version by type of surgical procedure (ileal conduit or neobladder). If adjustments of stratification are deemed necessary during the course of the trial, the trial protocol will be amended.

A fixed-sample design is planned. Changes of trial design, if necessary or advisable, resulting from an interim analysis without significance testing (no αspent) had to keep the prespecified significance level. In that case, the Brownian motion will be used for modeling the primary test statistic based on the accumulating data as a stochastic process (see next section).

The distributions will be described at all time points by median, minimum, maximum and quartiles separately for both the HES and HA groups.

The primary statistical analysis will be based on the intention-to-treat (ITT) principle.

Analysis of all secondary endpoints and of patient characteristics will be descriptive. Descriptive comparisons will be conducted with the *t* test or, in the case of deviations from the normal distribution, with the Mann-Whitney-Wilcoxon test, or with Fisher’s exact test in case of a binary outcome.

Safety data will be analyzed descriptively in the two groups at least every 12 months.

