#### Sensitivity analyses

After the primary ITT analysis, sensitivity analyses will follow per protocol or according to as-treated principles. In addition to the primary Mann-Whitney-Wilcoxon analysis, the Mann-Whitney-Wilcoxon test will be applied to the cystatin C values at day 90, and, assuming approximately normal distributions after log transformation (natural logarithm), explorative regression analyses will be performed modeling the log-transformed (natural logarithm) cystatin C values depending on treatment group, log-transformed (natural logarithm) baseline cystatin C values and other potentially prognostic factors.

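### The primary rank test on the day-90/baseline cystatin C ratio fixes the baseline slope at 1; under the protocol's own sizing model a baseline-adjusted rank test is at least as efficient, and the SD behind N = 94 rests on an unstated correlation

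*Protocol article*

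**What the plan says.** Under *Primary endpoint*, the protocol article defines the endpoint as day-90 cystatin C divided by the preoperative value. *Statistical analyses* plans a Mann-Whitney-Wilcoxon test on it, stratified by ileal conduit or neobladder, with no baseline covariate. The stated view there is that "The primary endpoint adjusts in a specific way for the preoperative cystatin C values". The same section chooses a rank test because normality is doubted even after taking logs.

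For the sample size, *Power considerations and sample size calculation* specifies "the value of 0.2222 for the standard deviation of the difference at day 90 minus baseline of the log-normal transformed cystatin C values", in both arms. Two reasons are given. First, the value is thought conservative for each arm at each time point. Second, relating day 90 to the patient's own baseline "is suggested to reduce rather than to increase the standard deviation". No within-patient correlation is stated.

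Baseline adjustment appears only under *Sensitivity analyses*, where "explorative regression analyses will be performed modeling the log-transformed (natural logarithm) cystatin C values depending on treatment group", log baseline and other, unnamed prognostic factors. *Interim analyses regarding confirmatory analysis* plans a roughly midcourse check of the sizing assumptions, with recalculation if they differ substantially.

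**The concern.** On the log scale the ratio is ln(day 90) minus ln(baseline), so baseline is subtracted with a slope fixed at 1. If the true slope is below 1, the subtraction brings in baseline noise that a fitted slope would leave out. Two things follow.

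- **Efficiency.** The confirmatory test may use the baseline measurement less well than it could, although cystatin C is scheduled at screening and at day 90 for every patient.
- **Support for the SD.** The first reason given covers only single-time SDs. The step from there to the SD of a change rests wholly on the second reason, which holds only under a condition on rho that the document does not state. The 80% power therefore carries a hidden assumption.

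**Working it through.** **Inputs (all from *Power considerations and sample size calculation*).** Two-sided 5% level and 80% power: "non-stratified Mann-Whitney-Wilcoxon test at a 0.05 two-sided significance level will have 80 % power". Effect: a GFR factor of 1.2, which "transfers to the detectable difference of 0.1368 for the log-transformed (natural logarithm) Cystatin C values". SD of the log change: 0.2222. Baseline mean 0.9 and SD 0.2 mg/L. 47 per arm. The model is normal on the log scale, without stratification. Rho is not given, so it is varied as an assumption.

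**Step 1: reproduce the plan.**
- Shift: ln(1.2)/1.333 = 0.1368.
- P = Φ(0.1368/(0.2222·√2)) = 0.6683.
- Noether's formula: N = (1.960 + 0.842)²/(3·(0.6683 − 0.5)²) = 92.4, so 47 per arm.
- Power at N = 94: Φ(√(3·94)·0.1683 − 1.960) = 0.807.
- Enrolment: 94/0.9 = 104.4, so 105.

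The stated figures are reproduced.

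**Step 2: where 0.2222 comes from.** 0.2/0.9 = 0.2222, the relative SD at one time point. With a common SD σ at both times, the SD of the log change is σ·√(2(1 − ρ)). This is at or below σ only if ρ ≥ 0.5, and it equals σ at ρ = 0.5. Using 0.2222 for both quantities therefore implies ρ = 0.5.

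**Step 3: baseline adjustment.** The residual SD after regressing ln(day 90) on ln(baseline) is σ·√(1 − ρ²). The ratio of residual variance to change variance is (1 − ρ²)/(2(1 − ρ)) = (1 + ρ)/2, which never exceeds 1. Apart from the small cost of estimating a slope, the ratio is never more efficient under this model.

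**Step 4: power at 47 per arm (σ = 0.2222, shift 0.1368, Noether).**

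| ρ (assumed) | SD of log change | Ratio test | Residual SD | Rank test on residuals | Total N for 80%, ratio | Total N for 80%, residuals |
|---|---|---|---|---|---|---|
| 0.3 | 0.263 | 67% | 0.212 | 84% | 127 | 85 |
| 0.4 | 0.243 | 74% | 0.204 | 87% | 110 | 79 |
| 0.5 | 0.222 | 81% | 0.192 | 90% | 92 | 71 |
| 0.7 | 0.172 | 95% | 0.159 | 97% | 58 | 50 |
| 0.8 | 0.141 | 99% | 0.133 | 99% | 40 | 37 |

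(N is the Noether value to the nearest whole number, before rounding up to equal arms.) Example at ρ = 0.3: 0.2222·√1.4 = 0.2629; P = Φ(0.1368/(0.2629·√2)) = 0.6435; power = Φ(√282·0.1435 − 1.960) = 0.674.

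Simulation with two strata and the van Elteren test (4,000 runs per ρ) gave 67% v 84% at ρ = 0.3, 81% v 90% at 0.5 and 96% v 98% at 0.7. Type I error was 4.2% to 5.7% for both tests.

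**Step 5: take the protocol's SD of change as correct.** If the SD of the log change really is 0.2222, the residual SD is 0.2222·√((1 + ρ)/2). Power then rises from 81% to about 90%, 86% and 84% at ρ = 0.5, 0.7 and 0.8. The gain does not need a low ρ.

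**The case against.** The strongest reply is that no error has been shown, and for the sample size that is right. A reader might infer that the trial is underpowered or that 94 is too few. The document does not support this. It gives no rho, so the rows at 0.3 and 0.4 are what-if cases. The SD was also set generously because subgroups are pooled and the patients are not healthy. Stable differences between patients cancel in a within-patient ratio, which would favour a higher rho.

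The 0.5 threshold also needs equal SDs. In general the change has a smaller SD than the day-90 value when ρ > SD(baseline)/(2·SD(day 90)), for example 0.33 if the day-90 SD is 1.5 times the baseline SD. If the common single-time SD were 0.20 (an assumed value), the change would stay within 0.2222 for ρ ≥ 1 − (0.2222/0.20)²/2 = 0.38.

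The interim check is real mitigation. A wrong SD of the log change can be seen there and N recalculated, with type I error protected by the conditional rejection probability method. It cannot recover the efficiency that the ratio gives up.

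A reader might also think that the planned regression could simply be promoted to primary. It is parametric and exploratory with an open covariate list, and the protocol doubts normality even on the log scale. The remedy has to be rank-based with fixed covariates, and that analysis is not yet planned.

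Finally, the ratio is a deliberate endpoint tied to the GFR ratio, and its test is valid. That stands: the matter is efficiency, not validity. The baseline data are not ignored either, since the sensitivity analyses use them.

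**Conclusion.** The point holds as one of efficiency plus an undocumented assumption. Under the protocol's sizing model (log-normal data, one SD of 0.2222 at both times), the ratio test is never more efficient than a baseline-adjusted rank test. At the implied rho of 0.5 the difference at 47 per arm is about 9 points of power (81% v 90%). It is larger at lower rho and negligible above about 0.8. The power gains are computed under normality on the log scale, which the protocol itself doubts, so they are indicative.

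Using 0.2222 for the change tacitly assumes a rho of at least 0.5 with equal SDs. That is unsupported. It would be a step too far to call it, N = 94 or the 80% power wrong.

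**What to change.** By amendment, before any comparative look at the data:

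1. Make the primary test a stratified (van Elteren) Wilcoxon test on residuals of ln(day-90 cystatin C) regressed on ln(baseline cystatin C) and procedure stratum. Leave treatment out of that regression, so that a permutation p value within strata remains available.
2. Keep the stratified test on the ratio as a sensitivity analysis.
3. Replace the argument that the ratio lowers the SD with the assumed rho, and show power over a range. For the ratio test at 47 per arm this is about 67% at 0.3, 81% at 0.5 and 95% at 0.7.
4. Have the planned interim check estimate both the SD of the log change and rho.

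No extra patients or measurements are needed. The cost is a mid-trial amendment of the confirmatory test in an open-label trial that began in May 2012, so its timing relative to any comparative look must be documented. The test would no longer be literally on the ratio, and the restated power of the ratio test falls below 80% over the lower part of the rho range.

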#### Sensitivity analyses

After the primary ITT analysis, sensitivity analyses will follow per protocol or according to as-treated principles. In addition to the primary Mann-Whitney-Wilcoxon analysis, the Mann-Whitney-Wilcoxon test will be applied to the cystatin C values at day 90, and, assuming approximately normal distributions after log transformation (natural logarithm), explorative regression analyses will be performed modeling the log-transformed (natural logarithm) cystatin C values depending on treatment group, log-transformed (natural logarithm) baseline cystatin C values and other potentially prognostic factors.

### Ethics and Good Clinical Practice

The trial will be conducted in accordance with the International Conference on Harmonization guidance regarding Good Clinical Practice, the relevant national regulations and the Declaration of Helsinki. The study protocol and consent forms were approved by the institutional review board of the Ludwig Maximilians University of Munich (reference number 311-11).

## Discussion

Despite the fact that there are several smaller clinical trials comparing HES to another fluid for volume replacement in various clinical settings, there is a general lack of evidence on the relative safety and effects of HES versus HA for volume replacement in a perioperative setting. Previously conducted studies of surgical patients in which researchers compared different HES products included too few patients for proper evaluation of clinically important outcomes such as renal function.

The present study will determine, in a high-risk patient population undergoing major surgical intervention, whether perioperative fluid replacement with HA has a long-term advantage over a third-generation HES (HES 130/0.4) on the progression to renal dysfunction until 3 months after surgery.

## Trial status

The study was initiated as planned in May 2012. The study is expected to be completed in February 2016.

## Appendix

**Table 1 Tab1:** Flowchart

Schedule of activities	Visit 1	Visit 2	Visit 3	Visit 4	Visit 5
	Screening day (day −1)	Day 0 (day of surgery)	Day 1	Day 3	Day 90
Informed consent	X				
Inclusion and exclusion criteria	X				
Demographic data	X				
Medical history (primary diagnosis)	X				
Pregnancy test for women of childbearing potential	X				
Mini Mental State Examination	X				
Life Quality Assessment (ADL, IADL)	X				X
Concomitant medications (diuretics)	X	X	X	X	X
Cystatin C, GFR, serum creatinine	X	X	X	X	X
ROTEM, Multiplate, PFA 100		X			
Randomization		X			
NGAL, syndecan 1, hyaluronan		X	X	X	
Study drug		X	X	X	
Blood products		X	X	X	
IV fluid amount		X	X	X	
Blood losses and urine output		X	X	X	
Nursing Delirium Screening Scale		X	X	X	
AEs and SAEs		X	X	X	X
Pruritus assessment					X

*ADL* activities of daily living, *AE* adverse event, *IADL* instrumental activities of daily living, *IV* intravenous, *NGAL* neutrophil gelatinase-associated lipocalin, *PFA 100* Platelet Function Analyzer 100, *ROTEM* rotational thrombelastometry, *SAE* serious adverse event2

**Table 2 Tab2:** Algorithm of infusions and transfusion in the operating room and intensive care unit

Hemodynamics	
ASA I and II patients without cardiac diseases or cerebral insufficiency:	
Stroke volume variation (SVV) <12 %	
Cardiac index (CI) > 2.5 L/min/m^2^	
MAD >60 mmHg	
ASA III and IV patients or patients with cardiac diseases or cerebral insufficiency:	
SVV <12 %	
CI >2.5 L/min/m^2^	
MAD >70 mmHg	
Central venous oxygen saturation >70 % or mixed venous oxygen saturation >65 %	
To reach the desired parameter:	
Start with infusion protocol (see below)	
If not successful within 15 minutes:	
Start with norepinephrine as first-choice vasopressor	
Infusion protocol	
Replacement of urine output with Ringer’s acetate solution in a 1:1 ratio	
Additionally, 500 ml of crystalloids for insensible sweating	
Replacement of blood and protein losses dependent on treatment assignment, with either HA 5 % or HES 6 % in a 1:1 ratio up to a transfusion trigger point or a maximum of 50 ml/kg/day	
Additionally up to 1500 ml of colloids for the protein loss into the third compartment

**Table 3 Tab3:** Transfusion protocol (in support of [24])

Red blood cells			
Hb (g/dl)	Risk factors	Transfusion	Evidence level
<6 g/dl	–	Yes	1c+
>6–8 g/dl	Adequate compensation, no risk factors	No	1c+
	Limited compensation or risk factors (cardiac diseases, cerebrovascular insufficiency)	Yes	1c+
	Signs of anemic hypoxia (tachycardia, hypotension, lactic acidosis, ECG change)	Yes	1c+
8–10 g/dl	Signs of anemic hypoxia (tachycardia, hypotension, lactic acidosis, ECG change)	Yes	2c
>10 g/dl	–	No	1a

*ADL* activities of daily living, *AE* adverse event, *ECG* electrocardiographic, *Hb* hemoglobin, *IADL* instrumental activities of daily living, *SAE* serious adverse event

**Table 4 Tab4:** RIFLE criteria as defined by Bellomo et al. [25]

Category	GFR criteria	Urine Output (UO) criteria
Risk	Increased creatinine × 1.5 or GFR decrease > 25 %	UO <0.5 ml/kg/h for 6 h
Injury	Increased creatinine × 2 or GFR decrease > 50 %	UO <0.5 ml/kg/h for 12 h
Failure	Increase creatinine × 3 or GFR decrease > 75 %	UO <0.3 ml/kg/h for 24 h or anuria for 12 h
Loss	Persistent ARF = complete loss of kidney function >4 wk	
ESKD	End-stage kidney disease (>3 mo)	

*ARF* acute renal failure, *ESKD* end-stage kidney disease, *GFR* glomerular filtration rate, *RIFLE* risk of renal dysfunction, injury to the kidney, failure of kidney function, loss of kidney function, and end-stage kidney disease, *UO* urine output

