Schabinski and colleagues compared the effect of 6 % HES 130/0.4 with 4 % gelatin on renal failure and mortality in critically ill surgical patients. They showed that a significant increase in mortality and acute renal failure occurred in the HES group if the cumulative dose of 33 ml/kg body weight was exceeded [5].

A survey of 120 Scandinavian intensive care units (ICUs) published in 2008 [6] revealed that, for most physicians, colloids are a second-choice volume substitute. Only one-third were found to use it as a primary volume substitute. HES 130/0.4 was the preferred colloid. A large part of the interviewees attested that there were no internal directives or contraindications for the use of HES at their centers. At the same time, almost all interviewees indicated that they would change their infusion practice if randomized controlled studies clearly showed negative effects on mortality and renal failure [6].

An alternative to HES is the use of human albumin (HA). The safety of HA was examined in the Saline versus Albumin Fluid Evaluation (SAFE) study, published in 2004 [7]. In that large investigation, the impact of saline 0.9 % and albumin 4 % was compared in critically ill patients. Neither in the whole group nor in one of the subgroups was a relevant difference found with regard to mortality, ICU length of stay, organ failure, respiratory support or renal replacement therapy. A post hoc analysis showed that the results were independent of the serum albumin value of the patients [8]. Indeed, in a subgroup analysis, the authors found an increase in mortality in patients with brain injury who received albumin compared with those in the saline group [9]. However, this was not a negative effect of the colloid albumin, but the result of volume loading in patients who are not hypovolemic and therefore without demand of any colloid infusion [10].

In a meta-analysis, Wilkes and Navickis investigated the safety of albumin and its influence on mortality. The authors compared 55 randomized trials in patients after major surgery, trauma, burn, hypoalbuminemia, ascites and other diseases. The researchers in the included trials compared albumin therapy with crystalloid therapy, no albumin or lower doses of albumin. Overall, the authors found no effect of albumin on mortality [11].

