### Hydroxyethyl starch 6 % 130/0.4 (Volulyte)

Blood and protein losses that occur during surgical procedures can be compensated by the patients up to a certain point. The current infusion practice is to provide a combination of crystalloid and colloid solutions. The objective is to reach hemodynamic targets and treat the diuresis of the patient to maintain sufficient organ perfusion. Guided by the hemoglobin values, blood transfusions are also used.

Protein and blood losses are currently substituted, at least in Central Europe, with HES. The common modern preparation is 6 % HES with a MW of 130 kDa and a substitution degree of 0.4 (Volulyte; Fresenius Kabi, Bad Homburg, Germany). This solution contains, in comparison with the serum value, higher sodium and chloride amounts (154 mmol/L in each case). According to the manufacturer, the maximum dose to be administered is 50 ml of hydroxyethyl starch/kg (i.e., 3500 ml for a patient of 70-kg body weight). This dose is based on experimental investigations in rats where the infusion of 9 g/kg HES showed no toxic effects. Information concerning the maximum dose to be administered in humans is absent.

Up to now, HES preparations of the modern generation were examined only in specified patient groups. No publication of a systematic investigation with information about maximum administrable dose exists in the literature. Therefore, it is unclear whether organ-toxic or coagulation-restraining effects, as proved with older HES preparations, also occur with use of the modern products.

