### Treatment groups

After screening and randomization, every patient is assigned to one of the two therapy arms:*VoluCyst study arm* (patients with cystectomy treated with HES): In this arm, patients receive 6 % HES 130/0.6 (Volulyte) perioperatively and up to the third postoperative day as the only colloid according to a treatment algorithm (see Appendix). The maximum dose according to the prescribing information is 50 ml/kg/day (e.g., 3500 ml for a patient with a body weight of 70 kg). Patients who require additional volume replacement therapy from day 3 until discharge will be treated primarily with HES, unless a contraindication to HES has emerged.*AlbuCyst study arm* (patients with cystectomy treated with HA): In this arm, patients receive 5 % HA (Humanalbin) perioperatively and up to the third postoperative day as the only colloid according to a treatment algorithm (see Appendix). Patients who require additional volume replacement therapy from day 3 until discharge will be treated with HA.

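### Table 2 caps loss replacement at 50 ml/kg/day and then allows up to 1500 ml more colloid, without saying whether this counts within the HES maximum the protocol cites

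*Protocol article*

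**What the plan says.** Table 2 in the Appendix has two consecutive colloid lines. The first replaces blood and protein losses 1:1 with HA or HES, according to allocation, "up to a transfusion trigger point or a maximum of 50 ml/kg/day". The second reads "Additionally up to 1500 ml of colloids for the protein loss into the third compartment". The limit is attached to the first line. The second line has a fixed volume that is not scaled to body weight, no time unit and no reference to the limit above it.

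The ceiling for HES appears in two other places. Treatment groups, in the HES arm description, says: "The maximum dose according to the prescribing information is 50 ml/kg/day (e.g., 3500 ml for a patient with a body weight of 70 kg". The product section on Volulyte gives the same worked volume without a time unit: "the maximum dose to be administered is 50 ml of hydroxyethyl starch/kg (i.e., 3500 ml for a patient of 70-kg body weight".

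Three further statements decide how these fit together:

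- Treatment groups makes HES the sole colloid in the HES arm perioperatively and through postoperative day 3, given by the Appendix algorithm.
- Methods/Design says the allocated fluid is given in line with the current prescribing information.
- The product section on Humanalbin says HA has no upper dose limit.

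**The concern.** Table 2 is the instruction that the team follows in the operating room and intensive care unit. Taken line by line, it lets a clinician reach 50 ml/kg of HES for losses and then give more HES under the next line. The main text names 50 ml/kg/day as the maximum and says that dosing follows the prescribing information. A clinician can therefore comply with the algorithm and still exceed the limit stated elsewhere in the same protocol.

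What is at stake is patient safety and a clear record of exposure. The Background describes the renal safety of HES as contested, and the primary endpoint is renal. HA has no stated upper limit, so the conflict with a cited maximum arises only in the HES arm.

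**Working it through.** **Inputs**

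- Cap on loss replacement: 50 ml/kg/day (Table 2).
- Further colloid: up to 1500 ml (Table 2).
- Cited HES maximum: 50 ml/kg/day, worked as 3500 ml at 70 kg (Treatment groups); the same volume appears in the Volulyte section.
- Body weight *w*: 70 kg is the protocol's example. The other weights below are assumptions chosen to show a range.

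**Reproducing the protocol's figure.** 50 ml/kg × 70 kg = 3500 ml, as stated.

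**Which colloid the second line means.** In the HES arm HES is the only colloid, so the additional volume must be HES.

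**Whether the second line is additive.** The same adverb opens the line that adds 500 ml of crystalloid to urine replacement, where it plainly means a separate volume. Nothing in the article places the 1500 ml inside the cap.

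**Upper bound, assuming both allowances are used in full on the same day**

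- Total = 50*w* + 1500 ml. At 70 kg: 3500 + 1500 = 5000 ml.
- Per kg = 5000 / 70 = 71.4 ml/kg.
- Excess over the cited maximum = 1500 / 3500 = 42.9%.

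**Point at which the maximum is passed if the full 1500 ml is given that day.** Loss replacement above 50*w* − 1500 ml. At 70 kg: 3500 − 1500 = 2000 ml, or 2000 / 70 = 28.6 ml/kg.

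| Weight (kg) | Cited maximum (ml) | Upper-bound total (ml) | ml/kg | Excess | Loss replacement at which the maximum is passed (ml) |
|---|---|---|---|---|---|
| 50 | 2500 | 4000 | 80.0 | 60% | 1000 |
| 60 | 3000 | 4500 | 75.0 | 50% | 1500 |
| 70 | 3500 | 5000 | 71.4 | 42.9% | 2000 |
| 80 | 4000 | 5500 | 68.8 | 37.5% | 2500 |
| 90 | 4500 | 6000 | 66.7 | 33.3% | 3000 |
| 100 | 5000 | 6500 | 65.0 | 30% | 3500 |
| 120 | 6000 | 7500 | 62.5 | 25% | 4500 |

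Because the 1500 ml is fixed, the possible relative excess is largest in light patients.

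**Alternative reading.** If 50 ml/kg/day is taken to cover all colloid, the total at 70 kg stays at 3500 ml and there is no excess.

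**The case against.** The strongest reply is that the ceiling is already in the main text. Treatment groups states the HES maximum without tying it to one indication, and Methods/Design commits to the prescribing information. On that view the 1500 ml line is an allowance beneath an overall cap, and Table 2 merely fails to repeat it. This reading is possible. But Table 2 does not state it, its wording points the other way, and a bedside algorithm should not depend on the user inferring a limit from another section. The existence of two readings is the reason to reconcile the text.

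The figures are also a theoretical maximum, and that limit stands. They need full use of both allowances on one day, although the 1500 ml has no time unit, and a transfusion trigger may end loss replacement earlier. The article gives no expected blood loss.

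Three stronger inferences are tempting but unsupported:

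- A reader might set the algorithm against the Background report of harm in critically ill surgical patients "if the cumulative dose of 33 ml/kg body weight was exceeded". That is a finding from another study, not a limit of this protocol. The Background also cites a cardiac surgery trial whose authors judged 50 ml/kg safe. It neither contradicts Table 2 nor supports a cumulative cap.
- A reader might conclude that exceedances would undermine the HA-versus-HES comparison. This is not shown: volume that Table 2 allows is not clearly a deviation, and the primary analysis is by intention to treat.
- A reader might want one limit for both arms. With no upper limit stated for HA, that would be a clinical decision, and the documents do not settle it.

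**Conclusion.** The point holds as an internal contradiction about the maximum dose of a study drug. Table 2 read literally permits more HES than the maximum cited in Treatment groups, and nothing in the article places the extra 1500 ml inside that maximum. At 70 kg the excess is at most 1500 ml, or 43% above 3500 ml, if both allowances are used in full on one day; it begins once loss replacement exceeds 2000 ml, if the full 1500 ml is given that day.

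The protocol does not direct anyone to exceed the maximum, and how often this would happen cannot be worked out from the article. The missing time unit in the Volulyte section is a minor, related inconsistency, since its worked volume agrees with Treatment groups. Sample size and error rates are unaffected. The point still needs correcting because it sits in the operative algorithm and bears on safety.

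**What to change.** Reconcile Table 2 with Treatment groups and Methods/Design. The text should state:

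- whether the additional colloid counts inside or outside the cited HES maximum;
- over what period the 1500 ml applies.

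Align the time unit in the Volulyte section at the same time. Which rule holds is for the clinical and regulatory leads; this review takes no position on it.

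The cost is a short amendment to the protocol and to the bedside algorithm. Trial status expected completion in February 2016. If enrolment has ended, the trial report should say which rule was applied and list any HES exposure above the cited maximum. The study-drug and intravenous fluid volumes that Table 1 already schedules on days 0, 1 and 3 can be used for this, so those days need no new data collection.
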